### Interim analyses {21b}

An interim analysis will be undertaken by multidisciplinary Data Safety Monitoring Board (DSMB) midway through the trial.

Additional ad hoc meetings may be scheduled if requested by either the CIs or the DSMB.

### Methods for additional analyses (e.g. subgroup analyses) {20b}

Post hoc subgroup analyses may be undertaken where there are differences between groups in relation to demographic and/or clinical characteristics.

### Methods in analysis to handle protocol non-adherence and any statistical methods to handle missing data {20c}

All randomised patient data will be analysed by intention-to-treat, regardless of treatment received. However, a per-protocol analysis for trial participants who consented, were randomised, completed the baseline assessment, and had at least one outcome assessment will also be conducted. Where enrolled participants do not have at least one outcome assessment (due to for example unexpected early discharge), they will be defined as “lost to follow-up”, regardless of their time in the trial. While all efforts are made to reduce loss to follow-up, as in most trials, it is inevitable that some missing outcome data may occur. In such circumstances, we envisage using best (no PI) and worst case (PI) scenarios to analyse the impact of missing outcome. These scenarios will form sensitivity analyses to assess the impact of missing outcome data, assuming those missing outcomes had no event or had an event.

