**Methods:**

This is a multicentre, pragmatic, parallel group, randomised controlled trial. A sample size of 1320 was calculated to have >90% power to detect a 5% difference in the primary outcome at an alpha of 0.05. Adult patients admitted to participating medical-surgical wards are screened for eligibility: ≥18 years, admitted to hospital within the previous 36 h, expected length of stay of ≥24 h, and assessed high risk for hospital-acquired pressure injury. Consenting participants are randomly allocated to either prophylactic silicone foam dressing intervention or usual care without any dressing as the control group via a web-based randomisation service independent of the trial. Patients are enrolled across three Australian hospitals. The primary outcome is the cumulative incidence of patients who develop a sacral pressure injury. Secondary outcomes include the time to sacral pressure injury, incidence of severity (stage) of sacral pressure injury, cost-effectiveness of dressings, and process evaluation. Participant outcomes are assessed daily for up to 14 days by blinded independent outcome assessors using de-identified, digitally modified sacral photographs. Those who develop a sacral pressure injury are followed for an additional 14 days to estimate costs of pressure injury treatment. Analysis of clinical outcomes will be based on intention-to-treat, per-protocol, and sensitivity analyses.

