### Criteria for discontinuing or modifying allocated interventions {11b}

#### Intervention

Where there is evidence of skin irritation and/or participant-reported discomfort and/or itchiness due to the dressing, the dressing will be removed, the skin reaction reported using standard hospital incident reporting protocols, and the patient exited from the clinical study. Where the patient has developed persistent urinary and/or faecal incontinence, the sacral dressing will be removed, and the patient exited from the clinical study. In our pilot trial, only six participants (5% of the total sample) reported dressing discomfort, due to dressing migration or mild itchiness without any other clinical symptoms of allergic reaction [13].

Note that in either group, diagnosis of a sacral HAPI resulting in the patient exiting the study will be made on a case-by-case basis in consultation with the clinician caring for the patient and/or the team leader. This decision will not influence the assessment of the outcome assessor (i.e. they will not be aware of the decision made by the clinician/team leader). Where there is indecision among the clinical staff caring for the patient regarding the diagnosis of a Stage 1 PI, the assessment by the blinded assessor will be used to determine if the patient should exit the clinical study.

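### The per-protocol set has no condition on continued dressing wear or on dressing use in controls; it is an available-case (modified ITT) set under the wrong name

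*Protocol article*

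**What the plan says.** The Abstract (Methods) names three bases for the clinical analysis: "Analysis of clinical outcomes will be based on intention-to-treat, per-protocol, and sensitivity analyses".

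Section {20c}, whose heading covers protocol non-adherence and missing data, gives the detail:

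- Intention-to-treat: "All randomised patient data will be analysed by intention-to-treat, regardless of treatment received".
- Then, introduced as a contrast: "a per-protocol analysis for trial participants who consented, were randomised, completed the baseline assessment, and had at least one outcome assessment".
- Patients who fail the last condition are labelled as losses to follow-up, in a sentence that begins: "Where enrolled participants do not have at least one outcome assessment (due to for example unexpected early discharge), they will be defined as".
- Missing outcomes: "we envisage using best (no PI) and worst case (PI) scenarios to analyse the impact of missing outcome". The section presents these as sensitivity analyses and does not say how missing outcomes enter the main ITT analysis.

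Other sections bear on adherence. Section {11a} has the dressing and skin inspected daily and dressing replacements documented with reasons; it also says that controls have no dressing applied. Section {11b} provides for removal with study exit. Table 1 lists dressing application under baseline data collection, and dose delivered and dose received under process evaluation. Section {31c} calls the article the full protocol.

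**The concern.** A per-protocol analysis is read as the effect among patients who were treated as allocated. Readers compare it with ITT to judge whether non-adherence diluted the effect. Here the contrast with an ITT analysis that ignores treatment received sets up that expectation, but the stated conditions do not meet it.

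The trial gives reasons to want such an analysis. Section {11a} expects dressings to roll, lose adhesion, become dislodged or be removed by accident. The Introduction says prophylactic dressings are increasingly used, so dressing use in controls is plausible. If the trial shows little benefit, the natural question is whether the dressing does not work or was not worn. The set as defined cannot help to answer it.

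This is not a detail left to an analysis plan. The protocol fixes a definition, and that definition does not fit its label.

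**Working it through.** **1. Whom each condition can exclude**

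| Condition in {20c} | Whom it can exclude |
|---|---|
| Consented | No properly enrolled patient: consent precedes randomisation ({26a}) |
| Randomised | Nobody in the ITT population |
| Completed baseline assessment | Patients with a missing baseline; possibly dressing patients whose dressing was never applied, if Table 1's baseline block counts as part of the assessment |
| At least one outcome assessment | Exactly those whom {20c} calls lost to follow-up |

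Two kinds of deviation exclude nobody: a dressing that lapses after baseline without being replaced, and a control who is given a sacral dressing. One outcome assessment is enough, so patients with partial follow-up stay in. Available-case is therefore the more exact term than complete-case.

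**2. Planning figures ({14})**

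Risks are 10% (control) and 5% (dressing), with 90% power and two-sided alpha 0.05. With unpooled variance:

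n = (1.96 + 1.2816)² × (0.10×0.90 + 0.05×0.95) / 0.05² = 577.9, so 578 per group as stated.

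The total of 1320 gives 660 per arm. A 10% loss leaves 0.9 × 660 = 594 assessed per arm.

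**3. What separates the set from ITT: missing outcomes**

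Risks among assessed patients are held at 5% and 10%, with 660 randomised per arm. The loss patterns are assumptions; the article gives only an overall allowance of 10%.

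| Loss, dressing / control | Set as written | ITT, missing = no injury | ITT, missing = injury |
|---|---|---|---|
| 10% / 10% | (29.7/594)/(59.4/594) = 0.50 | 29.7/59.4 = 0.50 | 95.7/125.4 = 0.76 |
| 15% / 5% | (28.05/561)/(62.7/627) = 0.50 | 28.05/62.7 = 0.45 | 127.05/95.7 = 1.33 |
| 5% / 15% | (31.35/627)/(56.1/561) = 0.50 | 31.35/56.1 = 0.56 | 64.35/155.1 = 0.41 |

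In the first row the 95% confidence intervals are 0.327 to 0.765 (set as written) and 0.326 to 0.766 (missing = no injury). An ITT analysis of observed outcomes equals the set as written in every row, apart from missing baselines. Adherence does not enter any of these figures.

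**4. What non-adherence does to the set as written**

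This is an illustration, because the article gives no non-adherence rate. Let a fraction q of assessed dressing patients be observed without a dressing after baseline, at the control risk of 10%. Then

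risk = 0.05(1 − q) + 0.10q, and RR = risk / 0.10.

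| q | Risk, dressing arm | RR, ITT among assessed | RR, set as written | RR, non-adherent patients excluded |
|---|---|---|---|---|
| 5% | 0.0525 | 0.525 | 0.525 | 0.50 |
| 10% | 0.055 | 0.55 | 0.55 | 0.50 |
| 20% | 0.060 | 0.60 | 0.60 | 0.50 |
| 30% | 0.065 | 0.65 | 0.65 | 0.50 |

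The control side behaves in the same way. If 10% of controls received a dressing and took the 5% risk, control risk would be 0.9×0.10 + 0.1×0.05 = 0.095, and RR = 0.05/0.095 = 0.526 in both analyses. It would be 0.50 with those controls excluded. The 0.50 figures assume that non-adherence is unrelated to risk.

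**The case against.** Several points on the other side stand.

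- **The set is not wholly blind to treatment.** Table 1 puts dressing application in the baseline block, so a patient whose dressing was never applied may already be excluded. The text does not settle this.
- **A dressing that comes off is not in itself a deviation.** Section {11a} provides for replacement after dislodgement or accidental removal.
- **Removal with exit follows the protocol.** On skin irritation or discomfort, "the dressing will be removed, the skin reaction reported using standard hospital incident reporting protocols, and the patient exited from the clinical study". Likewise: "Where the patient has developed persistent urinary and/or faecal incontinence, the sacral dressing will be removed, and the patient exited from the clinical study". If exit ends daily assessment, as the wording suggests, these patients add little undressed observation time. The illustration with q does not describe them.
- **Adherence is examined elsewhere**, through treatment fidelity ({11c}), the fidelity outcome ({12}), and dose delivered and received (Table 1). Nothing links these to the per-protocol set or to an effect estimate.

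Three stronger readings are tempting but not supported. A reader might infer that the set must reproduce the ITT result. That depends on how missing outcomes enter, as the unequal-loss rows show. A reader might also take the planned 10% attrition as the most by which the sets can differ, but it is a planning allowance and not a ceiling, and missing baselines come on top. Finally, the pilot report that "only six participants (5% of the total sample) reported dressing discomfort" might be turned into a count of non-adherent patients kept in the set. The article does not say that those dressings were removed, and under {11b} such patients exit as the protocol provides.

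Nor does the article say that this analysis will be used to judge adherence. False reassurance is a risk of interpretation, not a stated intention.

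**Conclusion.** The point holds as one of definition and labelling. Apart from possibly dropping patients whose dressing was never applied, the per-protocol set has no adherence condition in either arm. It is an available-case (modified ITT) set.

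Its agreement with ITT is near-automatic if the main ITT analysis uses observed outcomes, or counts missing as no injury with balanced loss. Any other difference comes from missing data. Under the assumed non-adherence of 5% to 30%, its relative risk moves from 0.525 to 0.65 in step with ITT, so it cannot isolate the effect among patients who kept to their allocation. Those rates, the loss patterns and the independence of non-adherence and risk are all assumptions. The structural conclusion rests on the wording of {20c} alone.

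The primary ITT analysis is unaffected. The correction is worth making because the Abstract names per-protocol as one of the three bases for the clinical analysis.

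**What to change.** 1. Rename the present set modified ITT (available-case), and say whether completing the baseline assessment includes application of the allocated dressing.
2. Before any unblinded analysis, define a supportive per-protocol set with criteria for both arms. Dressing arm: applied at baseline and maintained or replaced as the protocol provides, up to the endpoint or exit. Control arm: no prophylactic sacral dressing.
3. State that this set is selected after randomisation and is not protected by it, so it supports the ITT result and does not replace it.
4. State how missing outcomes enter the main ITT analysis, so that a difference between ITT and the available-case set can be interpreted.

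The cost is protocol or analysis-plan wording, with no change to design or sample size. The criteria can draw on the daily inspection, dressing-change and dose-received data as far as they record this. The article does not explicitly confirm a daily in-place record or a record of sacral dressings in controls, so the case report form should be checked first. If either is missing, the criteria should be limited to what was recorded, and that limit stated.

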### Sample size {14}

The sample size is based on the effect size reported in published research [2]. HAPI cumulative incidence in similar settings ranged from 4 to 13% in The Border Trial [8]. We based calculations on an expected effect of intervention on the primary outcome, calculated using a cumulative incidence ratio of 0.5 (0.46 in our pilot trial) [13], between groups. This assumed a cumulative incidence of 5% in the intervention group compared to 10% in the control group. To obtain 90% power with a two-sided *α* level of 0.05, a total 578 patients per group are required. To allow for attrition, a further 10% will be recruited with a total sample of 1320 (*n* = 220 per group/site).

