## Statistical methods

### Statistical methods for primary and secondary outcomes {20a}

The patient is the unit of measurement. The primary outcome, development of a new sacral HAPI, is dichotomous. The main analysis will be based on comparisons of the cumulative incidence of pressure injuries in the two groups. Relative risk (RR) of HAPI for the intervention group compared to the control group will be computed and reported along with 95% confidence intervals and *P* values.

We anticipate that prognostic imbalance of known (e.g. age, BMI, number of comorbidities) and unknown prognostic factors is unlikely between the groups due to central randomisation and treatment concealment. However, if we find any differences, we will conduct adjusted analyses using multiple regression models. We do not expect effect sizes to vary between hospitals, but centre-to-centre variability will be assessed, and cluster-adjusted analysis will be carried out as a form of sensitivity analysis if required. Patients’ declining to participate in the trial are given the opportunity to consent to some non-identifiable data being collected (i.e. admission type, age, sex, and PI risk score). These data will enable us to compare some characteristics of eligible and consenting patients (i.e. participants) versus patients who are eligible but not consenting (i.e. non-participants).

For the secondary endpoints, “time to HAPI” will be analysed using the Kaplan-Meier curve and log rank tests. Hazard ratios along with 95% confidence intervals will be reported. Additional Cox regression models will be used to detect the influence of prognostic factors. As for the “stage of HAPI”, a chi-square test will evaluate if the intervention group differs from the control patients. All data will be entered directly into a web-based data collection tool (REDCap) and then exported into SPSS (V 24). Prior to analysis, a rigorous process of data cleaning to check outlying figures, missing, and implausible data against source data will be undertaken. Sample attrition will be managed via intention-to-treat analysis to ensure an unbiased comparison of the groups by randomisation. An expert biostatistician will lead all analyses.

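### The best-case and worst-case scenarios give every missing outcome one value whatever the arm, so they do not bound the treatment effect; how early exits are scored is not stated

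*Protocol article*

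**What the plan says.** All places are in the protocol article.

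- Section {20c}, on non-adherence and missing data, sets the main analysis: "All randomised patient data will be analysed by intention-to-treat, regardless of treatment received".
- The same section gives the only definition of loss to follow-up, and it rests on having no assessment at all: "Where enrolled participants do not have at least one outcome assessment". Time in the trial does not enter into it.
- For missing outcomes it then says "we envisage using best (no PI) and worst case (PI) scenarios to analyse the impact of missing outcome", and describes these as sensitivity analyses "assuming those missing outcomes had no event or had an event".
- Statistical methods {20a} adds: "Sample attrition will be managed via intention-to-treat analysis to ensure an unbiased comparison of the groups by randomisation".
- Outcomes {12} names the difference in 14-day risk as the quantity to be tested. {20a} reports the relative risk.
- Observation can stop before day 14 for several reasons. Trial design {8} makes a new sacral injury, discharge and death the defined endpoints. Patients may also leave for a dressing reaction or persistent incontinence ({11b}, both under the intervention heading), by withdrawing consent, after which nothing more is collected ({26a}), or because clinical staff diagnose a stage 1 injury that the blinded assessor did not record ({18a}).

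**The concern.** In the two scenarios, best and worst describe the outcome value and not the direction of the treatment effect. If all missing outcomes are set to no injury, and then all to injury, both arms' risks move the same way each time. A sensitivity analysis of this kind is meant to show how far the missing data could shift the comparison. That requires letting the missing patients in the two arms differ, and neither scenario does so. With few events expected, the number of missing outcomes can match or exceed the number of observed events in the dressing arm, so the gap between the planned range and the full range is wide.

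Two related statements weaken the handling further. A patient with one assessment who then leaves because of a dressing reaction falls outside the definition of loss to follow-up, and the article does not say how that patient is scored. Dressing reactions can arise in one arm only. The sentence in {20a} also credits intention-to-treat with removing attrition bias. Intention-to-treat settles who is analysed in which arm; it does not supply outcomes that were never observed.

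**Working it through.** **Inputs.** Sample size {14}: "This assumed a cumulative incidence of 5% in the intervention group compared to 10% in the control group", 90% power, two-sided alpha 0.05, 578 per group, 10% for attrition, 1320 in total. With 1:1 allocation this is 660 per arm (220 × 3 sites). Two assumptions are mine: that missingness is equal in the two arms, and that the observed risks equal the planning risks.

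**The plan's own figure.** (1.960 + 1.282)² × (0.10 × 0.90 + 0.05 × 0.95) / 0.05² = 577.9, so 578 per group is reproduced.

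**Formulas.** Let N = 660 per arm, m = missing per arm, and a and b = observed events in the dressing and control arms.

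- All missing = no injury: RR = a/b.
- All missing = injury: RR = (a + m)/(b + m).
- Most favourable to the dressing: RR = a/(b + m).
- Least favourable: RR = (a + m)/b.

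**10% missing.** m = 66, so 594 are observed per arm; a = 29.7 and b = 59.4.

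| Scenario | RR | Risk difference |
|---|---|---|
| Planned, all no injury | 29.7/59.4 = 0.50 | -29.7/660 = -4.5 points |
| Planned, all injury | 95.7/125.4 = 0.76 | -29.7/660 = -4.5 points |
| Opposite by arm, favourable | 29.7/125.4 = 0.24 | -95.7/660 = -14.5 points |
| Opposite by arm, unfavourable | 95.7/59.4 = 1.61 | +36.3/660 = +5.5 points |

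With equal m, the risk difference is (a - b)/N in both planned scenarios because m cancels. On the scale that {12} names for the test, the two scenarios are then the same analysis as far as the estimate goes.

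With whole-number events (30 and 59 of 594) the planned pair is RR 0.51 (95% CI 0.33 to 0.78) and 0.77 (0.60 to 0.98). The unfavourable bound is 1.63 (1.20 to 2.21).

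**5% missing (assumed).** m = 33, a = 31.35, b = 62.7.

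- Planned: 0.50, and 64.35/95.7 = 0.67.
- Bounds: 31.35/95.7 = 0.33, and 64.35/62.7 = 1.03.

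**Unequal missingness (assumed), 5% and 10% observed risks, whole-number events.**

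- 90 missing on dressing and 42 on control: planned RR 0.45 and 1.14; bounds 0.27 and 1.90.
- 42 on dressing and 90 on control: planned 0.54 and 0.50; bounds 0.21 and 1.28.

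**Early exits after at least one assessment.** Suppose a share x of the dressing arm exits with a fraction f of its risk unobserved, true risks are equal, and the exits are scored as non-events. Then RR = 1 - x·f. For x of 5 to 10% and f of 25 to 75% this runs from 1 - 0.10 × 0.75 = 0.93 to 1 - 0.05 × 0.25 = 0.99. As an extreme, take 33 versus 66 events of 660. Counting 33 exits as events gives 66/66 = 1.00, and counting 66 gives 99/66 = 1.50.

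**The case against.** Several points can fairly be made for the plan.

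- **The wording is provisional and does not say both arms.** True. Arm assignment could be added in an analysis plan without contradicting {20c}. But the text defines best and worst by outcome value alone, and no scenario gives the arms opposite values, so the plain reading stands.
- **The planned scenarios are not inert.** They respond to differential missingness: with 90 versus 42 missing, the worst case crosses 1. Even at an equal 10%, the all-injury scenario is borderline (upper limit 0.98). So it cannot be said that the plan would always report robustness.
- **The bounds are far from likely values.** RR 1.61 needs an injury in every missing dressing patient and in no missing control. With 66 missing per arm and missing controls at 10%, control has 66 events. RR = 1 then needs 66 - 29.7 = 36.3 of the 66 missing dressing patients (55%) to be events. Losing p < 0.05 needs about 47 dressing events in total, or about 17 of 66 (26%), five times the observed 5%. This stands, and it is the argument for a tipping-point display.
- **Missing counts may be smaller.** The 10% is an allowance, the 5% is an assumption, and {18b} describes eligibility chosen so that at least one assessment is obtained.
- **Variable follow-up is partly met elsewhere** by the rate per 1000 bed days and the Kaplan-Meier and Cox analyses. These are secondary and do not settle the scoring of the primary outcome.

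A reader might also infer that early exits are counted as confirmed non-events in every scenario. The article does not say so. It defines loss to follow-up and is silent on how these exits are scored. For discharge or death without injury, non-event status follows from the trial's own endpoint.

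**Conclusion.** The point holds in a limited form. Read plainly, the two scenarios in {20c} do not bound the treatment effect. At 660 per arm, an equal 10% missing and risks of 5% and 10%, they span RR 0.50 to 0.76 with a constant risk difference, where the full range is 0.24 to 1.61. At an assumed 5% missing, the plan's 0.50 to 0.67 compares with 0.33 to 1.03. The size depends on the assumed amount and balance of missingness.

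The documents do not support the stronger claim that plausible missing data would reverse the result. Separately, the scoring of patients who exit after one or more assessments for a dressing reaction, incontinence, withdrawal or a clinician-only diagnosis is unstated. If they were scored as non-events, the bias under no effect would be modest (RR 0.93 to 0.99 on the assumptions above), though the extreme is large. The {20a} sentence on intention-to-treat claims more than that principle can deliver. All of this concerns a sensitivity analysis and its wording, and can be corrected without new data.

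**What to change.** 1. In {20c}, add the two opposite-by-arm scenarios (missing dressing = injury with missing control = no injury, and the reverse), or a tipping-point analysis that reports the imputed risks in each arm at which the conclusion changes, or both. The tipping-point form is more informative because it lets readers judge whether the required risks are credible.
2. State how the primary outcome is classified for patients whose observation stopped before day 14 for a reason other than pressure injury, discharge or death, and apply the same scenarios to them.
3. In {20a}, remove the claim that intention-to-treat ensures an unbiased comparison under attrition. Say only that patients are analysed in the arm to which they were randomised, and refer to {20c} for missing outcomes.

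Multiple imputation is an option but is not needed to repair this point. The cost is a few sentences, a little extra analysis, and a wider, possibly less favourable, sensitivity range in the report.
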